| Recruitment | Patients will be selected by ultrasound specialists after evaluation of their professional practices (EPP based on a tool implemented by CFEF [Collège Français d'Echographie Foetale - French college of foetal ultrasonography]) and sent to the investigators for inclusion in the study. |
| Exclusion period | There are no plans to exclude patients from participation in another clinical research other than a study on placental insufficiency. The exclusion period for studies of placental insufficiency ends within 72 hours of delivery. |
| Number of patients | 2,486 patients per arm, i.e. a total of 4,972 patients |
| Study duration | Duration of the inclusion period: **47 months**  Duration of participation for each patient: approximately 6 months  Total study duration: **53 months** |
| Expected benefits | To answer to the hypothesis of the efficacy of aspirin prescribed early (before the onset of trophoblast invasion) and at the highest dose proposed (in order to overcome a lack of efficacy by dose effect) in a "high-risk" subgroup of patients of 1/3 of primiparous women encompassing 75% of patients who will develop placental insufficiency. |

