## Expected duration of participation of persons and description of the timeline and duration of all test periods, including follow-up, where applicable

The duration of the study is estimated at **53** months (**47** months of inclusion and approximately 6 months of follow-up).

Note that patient follow-up is not fixed, it depends on the inclusion (between 11-15 WA) and the date of delivery.

From the first inclusion, the sponsor must inform the competent authority and the IEC, without delay, of the effective start date of the study (Effective start date = date of signature of the consent by the first patient taking part in the research)

The study end date will be sent by the sponsor to AFSSAPS and the IEC within 90 days. The research end date corresponds to the end of the participation of the last person to take part in the research, or, if applicable, **to the gestational age defined in the protocol.**

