## Exclusion criteria

No patient will be excluded from the study, after she has been randomised (intention to treat principle). However, premature termination is possible (see §10.2.1).

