Considering the risks of type 1 and 2 errors set at 5 and 20% respectively, we must include 2415 women per group (nQuery Advisor® 6.0).

Additionally, this study plans to carry out intermediate analyses. The hypotheses relating to the control group are poorly documented, which led us to rule out a triangular test experimental design. Indeed, we know that pooradvance knowledge of the success rate in the control group is potentially deleterious for the study (Sebille *et al*, Impact of a mis-specification of the response rate under standard treatment in sequential clinical trials. [*Fundam Clin Pharmacol*.](javascript:AL_get(this, 'jour', 'Fundam Clin Pharmacol.');) 2005;19:569-578). Finally, we decided to plan this study according to a Peto scheme (Peto R, Pike MC, Armitage P. Design and analysis of randomized clinical trials requiring prolonged observation of each patient. Br J cancer 1976;34:585-612. PMID).

Four intermediate analyses are planned, such that if the trial is discontinued after one of these intermediate analyses, the success rates associated with each of the groups are still accurately estimated. These intermediate analyses will be carried out every 1000 inclusions.

Carrying out an intermediate analysis leads to an increase in the total number of subjects to be included (if the study goes to its conclusion), such that the overall type I error (i.e. taking into account all the analyses) remains at the nominal value. Considering alpha at 5% and beta at 20%, the inflation parameter is 1.024 (Jennison *et al* (2000). Group sequential methods with applications to clinical trials. Chapman & Hall/CRC: Boca Raton), which leads us to include 2415*1.024 or 2473 patients per arm.

Finally, it is expected that for 0.5% [40] of women, the pregnancy will not be carried to term (medical termination of pregnancy). These women will not be taken into account in the primary analysis. We must therefore increase the number such that at the end of the study, we have 2473 analysable women per arm. This therefore leads us to include 2473/0.995 or 2486 women per arm.

Ultimately, 4972 women are expected to be included in this trial.

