## Primary endpoint analysis

Rates of pre-eclampsia during pregnancy or birth weight ≤ 5th percentile will be compared using a chi-square test. An adjustment for stratification factors will also be made as part of a logistic regression model.

Intermediate analyses (one every 1000 inclusions) will be performed at the thresholds of 0.001 and 0.049 for the last one (Peto rule).

The final analysis (if it needs to be carried out) will be conducted at the end of the 4972 inclusions. It will be performed at the 0.049 threshold, which means that a significant difference will be concluded only if the degree of significance is less than 0.049.

Finally, because intermediate analyses will be carried out, it will be necessary to adjust the estimates of the effect, the confidence interval of this effect, and the degree of significance. This will be achieved through implementation of the Lan & De Mets method (Discrete sequential boundaries for clinical trials. *Biometrika*. 1983;70:659-663).

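### If an interim look stops the trial, the only planned primary result leaves out women already randomised but not yet delivered

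*Protocol*

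**What the plan says.** Section 12.4 (Primary endpoint analysis) sets the stopping thresholds: "Intermediate analyses (one every 1000 inclusions) will be performed at the thresholds of 0.001 and 0.049 for the last one (Peto rule". It then places the last analysis: "The final analysis (if it needs to be carried out) will be conducted at the end of the 4972 inclusions". Section 12.1 counts the interim looks in the same unit: "These intermediate analyses will be carried out every 1000 inclusions". It adds that, if the trial stops at one of them, the rates in each group should still be accurately estimated. Section 12.4 closes by requiring the effect estimate, its confidence interval and the significance level to be adjusted for the interim looks by the Lan & De Mets method.

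The primary endpoint (section 7.1) combines pre-eclampsia, including postpartum onset, with birth weight, so it is complete only at or after delivery. Section 8.2 notes that "patient follow-up is not fixed, it depends on the inclusion (between 11-15 WA) and the date of delivery". The Abstract gives the timeline: "Duration of the inclusion period: 47 months", "Duration of participation for each patient: approximately 6 months", "Total study duration: 53 months". Section 9.3 states: "No patient will be excluded from the study, after she has been randomised (intention to treat principle".

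**The concern.** Outcomes arrive about six months after inclusion, so a block of randomised women is always awaiting delivery. If a look crosses 0.001, section 12.4 no longer requires a final analysis, and no section says what happens to that block in the primary result. Read as written, the deciding estimate is the interim one, computed without them.

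Two things are at stake. First, a result taken at the moment a boundary is crossed is on average too large. The pending women were not part of the data that triggered the stop, so adding them pulls the estimate back and improves precision. Second, with no rule fixed beforehand, whoever writes the report can choose between the interim and the complete dataset after seeing both.

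**Working it through.** **Inputs.** Event rates of 21.2% and 18.0%, 2415 per group, inflation factor 1.024, 0.5% medical terminations and 4972 in total (section 12.1). Thresholds of 0.001 at four looks and 0.049 at the end (section 12.4). Inclusion over 47 months, about 6 months per woman and 53 months in total (Abstract, section 8.2). Recruitment over 2½ years (section 19).

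**The plan's own figure.** A two-sided 5% comparison of 21.2% and 18.0% with 80% power, pooled variance and no continuity correction gives 2415 per group, as stated. Then 2415 × 1.024 = 2473, 2473 / 0.995 = 2485.4, rounded up to 2486 per arm, and 2 × 2486 = 4972.

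**Women pending at any time.** Assuming uniform accrual:
- 47 months: 4972 / 47 = 105.8 per month; × 6 = about 635.
- 30 months: 4972 / 30 = 165.7 per month; × 6 = about 994.
- With a lag of 5.5 to 6.9 months (an assumption), the ranges are 582 to 730 and 912 to 1144.

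**Share pending if a look is taken at the k-th inclusion (635 pending).**

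| Inclusions | Outcomes known | Pending |
|---|---|---|
| 1000 | 365 | 64% |
| 2000 | 1365 | 32% |
| 3000 | 2365 | 21% |
| 4000 | 3365 | 16% |

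**Effect on the estimate after an early stop.** Trials were simulated at 21.2% v 18.0% (true difference 3.2 points), stopping at two-sided p < 0.001. The difference was taken at the stop, then again after adding 635 pending women. The protocol does not say whether a look waits for outcomes, so both readings were run.

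| Looks based on | Chance of early stop | Mean difference at stop | With pending women added |
|---|---|---|---|
| Women delivered by the k-th inclusion | about 20% | 6.1 points | 5.3 points |
| 1000, 2000, 3000, 4000 known outcomes | about 26% | 5.6 points | 5.0 points |

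With 994 pending and looks on delivered women, the figures are 6.2 and 5.2 points. All are raw differences, before the planned sequential adjustment.

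Under the first reading the excess over the truth is 6.1 − 3.2 = 2.9 points, of which the pending women remove 6.1 − 5.3 = 0.8. Under the second it is 5.6 − 3.2 = 2.4, of which they remove 0.6. Most of the excess is therefore due to stopping early and not to the omission. Overall type I error stays at about 0.050 under either timing of the looks.

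**Full size.** With every woman followed to delivery, 4972 × 0.995 / 2 = about 2473 per arm are analysable, and power at 0.049 is 80.7%. If the test were literally run on the day of the last inclusion, (4972 − 635) × 0.995 / 2 = about 2158 per arm would remain, and power would be 75.2%.

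**The case against.** **Full size.** A reader might infer from section 12.4 that about 635 women, one in eight, are dropped from the final test even when the trial runs to completion, and that power falls to 75%. The protocol does not support that. Section 12.1 sizes the trial to have 2473 analysable women per arm at the end of the study and allows only for 0.5% medical terminations. The Abstract and section 8.2 add about six months of follow-up after the last inclusion, section 9.3 removes nobody, and a birth-weight endpoint cannot be scored before birth. The phrase about 4972 inclusions most naturally indexes the analysis by sample size, as the phrase about every 1000 inclusions does. This objection stands.

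**Early stop rests on silence.** A conditional final analysis is ordinary group-sequential wording. Nothing says that follow-up ends or data are discarded, section 12.2 refers to an analysis plan that is not to hand, and the supervisory committee may request further analyses (section 13.1.4). This stands in part: omission is implied and not ordered. But section 12.4 itself fixes when a final analysis is needed and provides no other primary result after a stop, so the gap lies in what the protocol states.

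**The planned adjustment already deals with exaggeration.** Section 12.4 does require the estimate to be corrected for repeated looks, so the raw differences above are not what would be published. The adjustment does not, however, bring in the outcomes of women who had not delivered.

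**The size depends on assumptions.** This also stands, which is why the pending number and the simulated differences are given as ranges.

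**Conclusion.** The point holds for an early stop. As section 12.4 is written, a trial stopped at 0.001 has only one planned primary result, and it excludes about 635 to 994 randomised women, contrary to the principle in section 9.3. At the design rates this would arise in about 20% to 26% of trials with 635 pending. The raw estimate would then be higher by about 0.6 to 0.8 points than with those women included. This is a modest part of the total excess over 3.2 points, but an avoidable one.

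These figures assume uniform accrual, a six-month lag and the protocol's own event rates. The range of 635 to 994 comes from two recruitment periods that the protocol does not reconcile.

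For a trial that runs to full size there is no loss of women or power as planned: power is about 81%. The timing phrase in section 12.4 is loose and should be aligned with sections 8.2 and 12.1.

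**What to change.** Replace the timing sentence in section 12.4 with wording to this effect:

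- The final analysis is performed once the primary outcome of the last randomised woman is known.
- If an intermediate analysis leads to stopping, all women already randomised are followed until their primary outcome is known. The primary analysis on all of them, with the planned sequential adjustment, is the main estimate. It is reported beside the interim result that triggered the stop and does not reopen the stopping decision.

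The last clause is needed because the p-value may rise above 0.001 once the pending women are added. The wording concerns follow-up and analysis only, not treatment after a stop.

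The cost is small: the women are already followed to delivery, so it is one extra run of the planned analysis and about six months' delay to the main report after an early stop.

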# Statistical considerations

## Number of patients to include

The population size is calculated as follows:

- pre-eclampsia occurs in 5-7% of primiparous women [19]
- the presence of bilateral notching and/or a high pulsatility index is predictive of the occurrence of pre-eclampsia, and this with a sensitivity of 75% and a specificity of 67% [28]

Hence, based on these data, out of every 100 primiparous women, the following numbers are expected to occur:

|  | Pre-eclampsia | No pre-eclampsia |  |
| --- | --- | --- | --- |
| Bilateral notching and/or high PI | 4.5 | 31 | 35.5 |
| No bilateral notching | 1.5 | 63 | 64.5 |
|  | 6 | 94 | 100 |

Thus, out of every 100 primiparous women, 35.5 women are expected to present with bilateral notching and/or a high pulsatility index, of which 4.5 will go on to develop pre-eclampsia.

The expected rate of pre-eclampsia in the control group is therefore 4.5/35.5 or 12.7%.

- Hypotrophy, defined by a birth weight ≤ 5th percentile, occurs more frequently in primiparous than in multiparous women [40]. Thus, although intrinsically (probabilistic definition of the disease), the prevalence of hypotrophy as defined is 5%, in primiparous women a rate of hypotrophy of approximately 7% is expected [43].
- the presence of bilateral notching and/or a high pulsatility index is predictive of the occurrence of hypotrophy, and this again with a sensitivity of 55% and a specificity of 67% [28].

Hence, based on these data, out of every 100 primiparous women, the following numbers are expected to occur:

|  | Hypotrophy | No hypotrophy |  |
| --- | --- | --- | --- |
| Bilateral notching and/or high PI | 3.85 | 31 | 34.85 |
| No bilateral notching | 3.15 | 63 | 66.15 |
|  | 7 | 94 | 100 |

Hence, out of every 100 primiparous women, 34.85 women with bilateral notching and/or a high pulsatility index are expected, of which 3.85 will give birth to a hypotrophic child.

The expected rate of hypotrophy in the control group is therefore 3.85/34.85 or 11.0%. Moreover, it is expected that for 20% of women developing pre-eclampsia we will also observe hypotrophy.

Thus, in the control group, we expect to observe [12.7 + (11.0-0.2*12.7)] or 21.2% of events (i.e. pre-eclampsia or hypotrophy).

Our hypothesis is that aspirin will reduce the occurrence of events by 15% [32]. The expected difference is therefore 3.2%, i.e. 21.2% of events are expected in the control group compared to 18.0% in the experimental group.

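### The adjustment for interim looks is assigned to a boundary method that does not produce adjusted estimates, and the statements on accuracy after early stopping and on sample size inflation do not fit the Peto design

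*Protocol*

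**What the plan says.** Protocol section 12.1 chooses a Peto scheme with four interim analyses, one every 1,000 inclusions, and a final analysis at 4,972. It says that if the trial stops at an interim, "the success rates associated with each of the groups are still accurately estimated". It then multiplies the fixed-design sample size by a factor taken from a group-sequential textbook: "the inflation parameter is 1.024". The boundary to which that factor belongs is not named.

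Section 12.4 sets the levels: the interim analyses "will be performed at the thresholds of 0.001 and 0.049 for the last one (Peto rule"). The next paragraph assigns the second level to the final analysis: "a significant difference will be concluded only if the degree of significance is less than 0.049". The section closes by saying that "it will be necessary to adjust the estimates of the effect, the confidence interval of this effect, and the degree of significance", and continues: "This will be achieved through implementation of the Lan & De Mets method". The reference given is the 1983 paper, whose printed title concerns discrete sequential boundaries.

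**The concern.** Three elements do not belong to one design. The thresholds are Peto, the inflation factor is not, and the adjusted inference is handed to a third method that serves another purpose. Alpha spending says how much type I error each look may use and so where the boundary lies. Once the Peto rule has fixed the boundary, that task is done. An adjusted estimate, interval or p-value needs a further choice, such as an ordering of the sample space, and the protocol makes none.

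The two sections also disagree. Section 12.1 treats estimates after early stopping as accurate, while section 12.4 says they must be corrected. What is at stake is the reported effect if the trial stops early. Stopping at p < 0.001 selects trials with unusually large observed differences, and the correction named for this would not deliver one.

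**Working it through.** **Inputs.** Section 12.1: "21.2% of events are expected in the control group compared to 18.0% in the experimental group"; alpha 5% and power 80%, giving 2,415 per group; factor 1.024; 0.5% not analysable. Sections 12.1 and 12.4: looks at 1,000, 2,000, 3,000, 4,000 and 4,972, with level 0.001 at the four interims and 0.049 at the final. Sidedness is not stated. Two-sided is assumed because it reproduces 2,415 (one-sided gives 1,902).

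**1. The plan's own sample size.** n = [1.960·√(2·p̄·q̄) + 0.8416·√(p₁q₁ + p₂q₂)]² / d², with p̄ = 0.196 and d = 0.032.
- √(2 × 0.196 × 0.804) = 0.5614; × 1.960 = 1.1003.
- √(0.212 × 0.788 + 0.18 × 0.82) = 0.5609; × 0.8416 = 0.4721.
- (1.1003 + 0.4721)² / 0.032² = 2.4725 / 0.001024 = 2,414.6, so 2,415 per group. This matches.
- 2,415 × 1.024 = 2,472.96, so 2,473. 2,473 / 0.995 = 2,485.4, so 2,486. Twice that is 4,972. This matches.

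**2. Thresholds.** Recursive numerical integration at information fractions 0.201, 0.402, 0.603, 0.805 and 1:
- Four looks at 0.001 plus a final at 0.049 give overall two-sided alpha 0.0501.
- The exact final level for 0.05 is 0.0489, which rounds to the printed 0.049. The thresholds are Peto and they hold.

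**3. Inflation factor at 80% power, same integration.**

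| Design | Factor |
| --- | --- |
| Stated Peto design, five analyses | 1.0043 (1.0047 with the exact final level) |
| Peto type with \|Z\| ≥ 3 at interims, five analyses | 1.015 |
| O'Brien-Fleming, four analyses | 1.0238 |
| O'Brien-Fleming, five analyses | 1.028 |

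The printed 1.024 matches O'Brien-Fleming with four analyses. The plan has five analyses and a different boundary. With 1.0047, 2,415 × 1.0047 is about 2,427 analysable, and 2,427 / 0.995 is about 2,439 included per arm. That is about 47 fewer than 2,486 (47 / 2,486 = 1.9%). Power of the plan as written, at 2,473 analysable per arm, is about 80.8%.

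**4. Estimates after an early stop.** 300,000 trials were simulated at 21.2% against 18.0%, with 500, 1,000, 1,500, 2,000 and 2,473 per arm at the five analyses and the stated levels. The smallest difference that crosses an interim boundary is about 3.29 × √(2 × 0.196 × 0.804 / n per arm).

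| Look | Needed to cross (points) | Chance of stopping here | Mean observed difference (points) |
| --- | --- | --- | --- |
| 1 | 8.3 | 2.1% | 9.2 |
| 2 | 5.8 | 5.5% | 6.5 |
| 3 | 4.8 | 8.4% | 5.3 |
| 4 | 4.1 | 10.2% | 4.6 |
| Any interim | – | 26.3% | 5.6 |

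The true difference is 3.2 points, so the early-stop mean overstates it by 5.58 / 3.2 − 1 = 74%. The mean group rates after an early stop are 22.4% and 16.8%, against true values of 21.2% and 18.0%. Every interim boundary lies above 3.2 points, so any trial stopped early for benefit reports more than the planned effect.

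**5. If accurate means only precise.** At look 1 each rate has a 95% half-width of 1.96 × √(0.196 × 0.804 / 500) = 3.5 points. That is wider than the 3.2-point difference the trial is built to detect.

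**The case against.** The sentence in section 12.1 may be meant only to explain the spacing of the looks, that is, as a statement on precision. Each group rate is off by only about 1.2 points after an early stop. Over all trials, stopped or not, the mean difference is 3.5 against 3.2 points, and the 9.2-point figure concerns about 2% of trials. Section 12.4 shows that the authors knew adjustment was needed. The exact algorithm would normally sit in the analysis plan to which section 12.2 refers. The inflation error makes the trial slightly larger, not smaller. All of this lowers the weight of the point. It does not remove it: the protocol does not leave the method open but names one that does not do the job, and the accuracy sentence fails on precision too at look 1.

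A reader might infer more than the document supports:
- That the thresholds fail the Peto rule. They do not; overall alpha is 0.0501.
- That the fourth interim is tested at 0.049, which with the final at 0.049 would give overall alpha 0.070. The sentence taken alone allows this, but the next paragraph ties 0.049 to the final analysis.
- That significance is corrected twice, with an adjusted p-value judged at an already lowered level. The document states the test first and introduces adjustment afterwards; it does not say that the adjusted p-value is the one tested. Even on that reading, only nominal p-values between about 0.0479 and 0.049 would change verdict.
- That the trial is underpowered because of the factor. At the printed rates it is not.

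**Conclusion.** The concern holds in three limited parts. First, section 12.4 assigns adjusted estimation to a boundary method that does not itself supply it. Second, the claim in section 12.1 that rates remain accurate after an early stop is wrong and conflicts with section 12.4: about one trial in four would stop early at the planning rates, with a mean difference of 5.6 points against 3.2. Third, 1.024 is not the factor for the stated design (about 1.004), an error of roughly 47 women per arm on the safe side.

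Type I error is controlled, and power is about 80.8%. The practical consequence is confined to reporting after an early stop, so the weight is modest. The figures assume two-sided testing, the printed event rates, and known outcomes for all women counted at each look.

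**What to change.** Keep the looks, the Peto thresholds and the 4,972 women.

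- State that the significance decision rests only on the nominal p-value: below 0.001 at each of the four interims, below 0.049 at the final analysis.
- Replace the Lan-DeMets sentence with a method that gives sequentially adjusted inference, for example a median-unbiased estimate, confidence interval and p-value under stage-wise ordering. Report these alongside the nominal result and do not test them a second time. Reading the adjusted p-value against its own limit would create two rules that can disagree: a nominal 0.049 has a stage-wise value of 0.0501.
- Delete the sentence in section 12.1 that rates remain accurate after an early stop.
- Restate the inflation as about 1.004, or keep 2,473 analysable per arm and state power as about 80.8% under the printed rates.

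The cost is a few sentences and a little extra analysis, with no change to recruitment or to the interim schedule.
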